### Trial objectives

This designed randomized controlled trial will explore the efficacy of alendronate sodium vitamin D_3_ compared to placebo on the improvement of joint structure and pain in patients with knee osteoarthritis. Our primary hypothesis is that there will be a significant improvement in the joint structure, as measured by the WORMS scale, in favor of alendronate at each assessment timepoint. Our secondary hypothesis is that there will be a significant improvement in knee pain, severity of OA, and quality of life, as well as a significant reduction in the level of inflammatory biomarkers, among patients assigned to the alendronate sodium vitamin D3 as compared to those given placebo.

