## Methods/design

### Study design and setting

This is a multicenter, randomized, double-blinded, placebo-controlled study. Upon obtaining Institutional Review Board (IRB)- Ethics Committee’s approval (from each corresponding included center), recruitment of patients will begin. The study is scheduled to start on May 1, 2021, with a completion date on December 31, 2022. Patients will undergo a 1:1 double-blinded randomization to receive a one-year course of alendronate sodium vitamin D_3_ tablets (Gubangjia, The CSPC Ouyi Pharmaceutical Co., Ltd. Shijiazhuang, China) or placebo. The use of Tylenol for pain control will be permitted during the trial; however, it will be monitored and reported for future analysis. In addition, Vitamin D and calcium supplementation will be allowed for usage by study participants. The use of unmarketed drugs or other investigational drugs will be prohibited during the study period; otherwise, such patients will be excluded. Other bisphosphonates (such as zoledronic acid, risedronic acid, etc.) will be prohibited during the study period. Non-steroidal anti-inflammatory drugs and other topical drugs with analgesic effects will be prohibited during the study period. This study will be carried out in three domestic hospitals (Peking Union Medical College Hospital, Zhongshan Hospital of Fudan University, and The Third Affiliated Hospital of Southern Medical University) with a follow-up period of 2 years.

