#### Secondary outcomes

We have seven pre-identified secondary outcomes: WORMS score (at 24 months), pain intensity (at 2, 4, 8, and 12 weeks after enrollment), quality of life (QOL), bone density, risk of knee replacement, severity of knee OA, and estimation of inflammatory biomarkers.The structure of knee joint will be measured using the WORMS scale at 24 months after treatment.Knee pain will be measured in both groups at 2, 4, 8, and 12 weeks after enrollment using the 100-mm visual analogue scale (VAS), which has already been shown to be valid and reliable in measuring pain [21]. Overall ratings range from 0 to 100 mm, where 0–4 mm indicate no pain, 5–44 mm indicate mild pain, 45–74 mm indicate moderate pain, and 75–100 mm indicate severe pain.Quality of life in both groups will be assessed at 3, 6, and 12 months after enrollment using the previously validated Chinese version of the SF-36 questionnaire [22], which is used to measure health status based on eight categories: (1) physical activity, (2) social activity, (3) physical role, (4) energy and emotional status, (5) mental health, (6) vitality, (7) body pain, and (8) general health. The overall score ranges from 0–100, with higher scores reflecting better health-related QoL [23]. This version of the SF-36 questionnaire shows comparable validity and reliability to the original version.Bone density of the lumbar spine and the hip and knee joints will be carried out using dual-energy x-ray absorptiometry (DXA) at 12 and 24 months after enrollment. Bone density data will be obtained using a Prodigy DXA scanner (GE Healthcare, Madison, USA) and the obtained data will be analyzed according to the manufacturer’s software. The lumbar spine (L1-L4) and the hip (particularly the femur neck and total hip) will be scanned in the supine position using posteroanterior projections.The risk of knee replacement will be evaluated based on a set of baseline and clinical variables and then incorporated into a multivariable logistic regression model to identify significant predictors of knee replacement in patients with OA.Severity of OA will be measured at 12 and 24 months after enrollment using the Kellgren-Lawrence grading scale [24]. The scores of this grading scale range 0 to 4, where 0 indicates no features of OA, 1 indicates questionable osteophytes, 2 indicates definite osteophytes without narrowing in the joint space, 3 indicates definite osteophytes with moderate narrowing, and 4 indicates definite osteophytes with severe narrowing.The serum level of the following inflammatory biomarkers will be measured at 3, 6, and 12 months after enrollment: interleukin (IL)-6, tumor necrotic factor (TNF)-alpha, erythrocyte sedimentation rate (ESR), and C-reactive protein (CRP).

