### Sample size calculation

Based on a previous observation, the mean annual loss of the medial tibial cartilage volumes in knee OA patients is 4.5% [25]. The monthly intake of vitamin D (50,000 IU) would result in a serum vitamin D3 level > 60 nmol/L [26], and this, in turn, has been reported to correlate with a 2.2% annual absolute reduction in cartilage loss [27]. This can be translated into a risk reduction of 22% for knee replacement over a period of 2 years [28]. Our sample size calculation was conducted based on Cohen’s formula [29]. With a power level of 80% and alpha level of 0.05, 60 participants (30 in each group) were required to detect a 2.2% between-group difference in terms of medial tibial cartilage loss (WORMS scale) during the second assessment time-point (12 months). Losses to follow-up were not considered in our initial sample size calculation (*NCT04739592*); however, given the fact that both interventions will be administered for a year and patients will be followed up for 2 years after enrollment, we anticipate that around 10% will be lost to follow-up each year, so we increased our final sample size to 220 participants (110 in each group).

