### Statistical analysis

Retrieved data from each patient in both groups will be recorded at baseline and at each follow-up assessment period using Excel, which will then be entered into a software for analysis after the final assessment point has been met. All statistical analysis will be conducted by a third-party (not involved with our research in any way) using the Statistical Analysis System (SAS) Software for Windows (version 9.4, *SAS institute, USA*).

Baseline demographic and clinical variables will be presented in the form of number and percentages for categorical variables, while continuous variables will be presented as means and standard deviations (SD) or median and range if the data were normal or skewed, respectively.

Our primary outcome will be analyzed with the intention-to-treat (ITT) analysis and reported as the mean difference (MD) and corresponding 95% confidence interval (CI) in cartilage-WORMS score between the intervention and control groups using Student’s t-test. Secondary outcomes will then be analyzed at the final assessment. Pain will be analyzed as a categorical outcome using the chi-square test, while the differences in continuous determinants of pain (baseline variables) will analyzed using MANOVA test. The QoL will be analyzed and reported as the mean difference and its corresponding 95% CI between both interventions using t-test. Bone density and osteoporosis severity (measured by the Kellgren-Lawrence scale) will be analyzed as categorical outcomes (normal, low density, osteoporosis) using the Chi-square test. Meanwhile, differences in serum levels of inflammatory biomarkers between both groups will be measured using t-test. In order to account for missing data, survival analyses will be conducted while implementing the “last-observation carried forward” approach. Such data will be presented in Kaplan–Meier curves, showing the numbers of patients analyzed at each assessment timepoint. A *p*-value of less than 0.05 will indicate statistical significance.

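### The MANOVA for determinants of pain puts the baseline variables on the outcome side with no grouping factor named, and neither plausible grouping shows which variable is related to pain

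*Protocol article*

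**What the plan says.** The Statistical analysis section of the protocol article treats pain in one sentence with two parts. The first part is the comparison of pain itself: "Pain will be analyzed as a categorical outcome using the chi-square test". The categories are presumably the VAS bands under Secondary outcomes: "0–4 mm indicate no pain, 5–44 mm indicate mild pain, 45–74 mm indicate moderate pain, and 75–100 mm indicate severe pain". The second part is the one at issue: "the differences in continuous determinants of pain (baseline variables) will analyzed using MANOVA test".

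The sentence fixes the method (MANOVA) and the variables (continuous, measured at baseline). It does not say which groups are compared. It also describes no test or adjustment for individual variables. The general threshold is a p-value "less than 0.05 will indicate statistical significance".

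Elsewhere the article handles a similar question differently. For knee replacement, Secondary outcomes plans a multivariable logistic regression in which knee replacement is the response and baseline and clinical variables are the predictors.

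**The concern.** A determinant of pain is a variable that helps to explain pain, so the natural model has pain as the response and the candidate variables as predictors. A MANOVA of baseline variables does the opposite: they form the dependent vector, and the null hypothesis is that their mean vectors are equal across groups. Pain cannot be in that vector, because the same sentence makes it categorical. Pain can enter only as the grouping factor, or not at all.

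The article leaves the analysis to a third party, who would have to choose the factor. If the choice is treatment arm, the output is a check of baseline balance, and a chance rejection could be mistaken for failed randomisation. If the choice is pain category, a significant result says only that at least one variable, or a combination of them, is associated with pain. Neither output supports a statement about one variable, and neither uses the baseline data to sharpen what is learned about pain.

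**Working it through.** The plan gives no figure for this analysis, so there is none to reproduce. The check takes each possible grouping factor in turn and sizes the consequence by simulation.

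**Inputs from the article**
- Allocation: "Patients will undergo a 1:1 double-blinded randomization" (Study design and setting).
- Sample sizes (Sample size calculation): "With a power level of 80% and alpha level of 0.05, 60 participants (30 in each group) were required", and then "we increased our final sample size to 220 participants (110 in each group"). Both N = 60 and N = 220 were run.
- Pain categories: the four VAS bands, with no pain and mild pain merged because the lowest band is sparse. Significance level 0.05.

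**Assumed inputs (not in the documents)**
- Two standard normal baseline variables, x1 and x2, with correlation ρ = 0, 0.3, 0.5 or 0.7.
- VAS = 45 + 8·x1 − 8·arm + error, error SD 18 mm, limited to 0–100. Thus x1 is a true determinant and x2 has no effect. Within an arm, the correlation of x1 with VAS before truncation is 8/√(8² + 18²) = 8/19.70 = 0.41.
- A second set of runs sets the effect of x1 to zero.
- 3,000 runs per scenario, so the Monte Carlo standard error at a 5% rate is √(0.05 × 0.95/3000) = 0.4 percentage points.

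**Reading (a): groups are the treatment arms.** The null is E(x1, x2 | active) = E(x1, x2 | placebo). Both variables precede randomisation, so it is true by design. The Wilks test rejected in 4.0–5.7% of runs over all 16 scenarios, with x1 affecting pain or not. The result does not depend on pain.

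**Reading (b): groups are pain categories.** The null is that the mean vector (x1, x2) is equal in every pain category.
- With no true determinant the omnibus test rejected in 4.6–5.6% of runs, so its size is correct.
- With x1 a true determinant it rejected in 53–55% of runs at N = 60 and about 99% at N = 220. That is power for a global question; it does not point to x1 rather than x2.

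**Naming individual variables under (b).** This needs a further step, which the article does not describe. The obvious one is a one-way ANOVA of each variable by pain category. The table shows how often x2, which has no effect, is flagged when x1 is a true determinant.

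| ρ | ANOVA, N = 60 | ANOVA, N = 220 | Regression of VAS on x1, x2 and arm |
|---|---|---|---|
| 0 | 5% | 5% | about 5% |
| 0.3 | 11% | 24% | about 5% |
| 0.5 | 18% | 60% | about 5% |
| 0.7 | 35% | 89% | about 5% |

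The regression column covers both sample sizes (range 4.4–5.5%). The same regression found x1 in 65–90% of runs at N = 60 and 99.6–100% at N = 220.

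**Sensitivity.** With a stronger determinant (correlation 0.5 with week-12 VAS, four baseline variables), the false-flag rates at ρ = 0.3 and 0.5 were 34% and 78% at N = 220, and 13% and 30% at N = 60. The direction is the same and the size moves with the assumptions.

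**The case against.** The best defence is that the omnibus MANOVA by pain category is not wrong. Wilks' lambda depends only on the canonical correlations between the two sets of variables, so the joint test is the same whichever set is called dependent, and its size is correct. This stands: having the baseline variables on the outcome side does not invalidate the global test. What remains is that a global test does not answer a question about individual variables.

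A reader might infer that the plan will report false determinants. The documents do not support that. The excess needs per-variable follow-up tests, which the article does not mention, and a no-effect variable correlated with a true determinant. At zero correlation the rate is 5%.

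A reader might also infer that the MANOVA costs power for the treatment comparison of pain. It does not, because the chi-square test carries that comparison. The stated aim, "Our secondary hypothesis is that there will be a significant improvement in knee pain, severity of OA, and quality of life", concerns the effect of treatment, and no objective or listed secondary outcome is to identify determinants of pain.

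Finally, a condensed article may leave the grouping factor and the variable list to a fuller document. That is fair for the missing detail taken alone. It does not remove the point, because the article commits to a named test, and filling in either factor still leaves a test that does not match its target.

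**Conclusion.** The point holds as a minor one. The planned MANOVA does not fit the question of which baseline variables determine pain. Grouped by arm it tests only chance imbalance, with about 5% rejection whatever drives pain. Grouped by pain category it is a valid global test of association that cannot separate one variable from another or adjust for arm.

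The first statement follows from randomisation and the second from the MANOVA null hypothesis; neither needs the simulation. The false-flag rates are conditional on unadjusted follow-up tests and on the assumed effects and correlations, and should be read as an illustration of what could follow, not as a forecast for this trial.

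The analysis is ancillary. The primary WORMS comparison and the sample size do not depend on it. Whether the chi-square test is a good choice for comparing pain between arms is a separate matter.

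**What to change.** Replace the MANOVA with one linear regression. Suggested wording:

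> Determinants of pain will be explored in a linear regression with the 12-week VAS score (continuous, in mm) as the response, and treatment arm, baseline VAS and the other baseline variables named before unblinding as predictors. Coefficients will be reported with 95% confidence intervals, and the determinant estimates will be labelled exploratory. Baseline variables will be summarised by arm and not tested.

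Candidates for the other variables include age and the baseline cartilage WORMS score. Week 12 is the last pain assessment under Secondary outcomes, so it agrees with the plan to analyse secondary outcomes at the final assessment. The structure also matches the outcome-as-response regression already planned for knee replacement.

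The cost is a change to one sentence of the analysis text and a few lines of SAS, with no new data or patients. The small downside is that the covariates must be fixed before unblinding.

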### Eligibility criteria

#### Inclusion criteria

Patients will be eligible for inclusion if they are consistent will all of the following criteria: (1) adult patients (50–75 years of age) with significant knee pain (defined as pain score ≥ 40 mm on the 100mmVAS scale), (2) having a diagnosis of knee osteoarthritis per the diagnostic criteria of the American College of Rheumatology (ACR) and the Chinese Orthopedic Association, and (3) having a radiographic Kellgren-Lawrence grade I or II knee OA and MRI findings of bone marrow edema-like lesions. The inclusion of bone marrow edema-like lesions (identified by high bone turnover through MRI) is because they are associated with greater response to bisphosphonates [19].

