#### Limitations:

Follow-up for knee replacement will be over a period of 2 years which may not be long enough in patients with early osteoarthritis.Although this study will provide guidance regarding the effects of alendronate, we will not be able to determine the ideal treatment length for osteoarthritis.

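### Kellgren-Lawrence grade is analysed under an osteoporosis label with bone-density classes, DXA only as three classes, and knee replacement without a stated comparison between arms

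*Protocol article*

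**What the plan says.** Three of the seven secondary outcomes are involved.

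- **KL grade.** Secondary outcomes states: "Severity of OA will be measured at 12 and 24 months after enrollment using the Kellgren-Lawrence grading scale". It adds that "The scores of this grading scale range 0 to 4", with grades defined by osteophytes and joint-space narrowing. Entry requires "having a radiographic Kellgren-Lawrence grade I or II knee OA".
- **Bone density.** Secondary outcomes plans DXA of the spine, hip and knee at 12 and 24 months.
- **Analysis of both.** Statistical analysis treats them in one sentence: "Bone density and osteoporosis severity (measured by the Kellgren-Lawrence scale) will be analyzed as categorical outcomes (normal, low density, osteoporosis) using the Chi-square test". The same section places the secondary analyses at the final assessment. It gives the WORMS score and quality of life a mean difference with a 95% CI.
- **Knee replacement.** Its only stated analysis is in Secondary outcomes, where baseline and clinical variables are "incorporated into a multivariable logistic regression model to identify significant predictors of knee replacement in patients with OA". Statistical analysis does not mention it. The Limitations section concedes: "Follow-up for knee replacement will be over a period of 2 years which may not be long enough in patients with early osteoarthritis".

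**The concern.** Severity of osteoarthritis is part of the trial's secondary hypothesis, and the Abstract also lists radiographic progression as an endpoint. The one sentence that fixes the KL analysis names another disease and gives classes to which no KL grade corresponds. An outside party with no role in the research is to run the analysis, so the text should be executable as it stands.

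Bone density is measured on a continuous scale, yet only class membership is tested. A patient whose density changes within a class adds nothing to that test. The reader would get a p-value without a difference in density or its precision.

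For knee replacement, a model that looks for predictors answers a prognostic question. The sample size section cites a reduction in replacement risk ("This can be translated into a risk reduction of 22% for knee replacement over a period of 2 years"), so readers will look for a comparison between arms, and none is stated.

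**Working it through.** The plan gives no power or sample size for these outcomes, so there is no figure to reproduce. The textual defects need no arithmetic. The calculations below are illustrations.

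**Inputs from the article.** 110 per arm and about 10% lost per year for two years. Taking 20% off, 110 × 0.80 = 88 per arm (compounding gives 110 × 0.81 = 89). Entry at KL I or II; two-sided alpha 0.05 (the article does not state sidedness).

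**Assumptions, not in the article.** One-grade KL progression of 25% versus 10%; a DXA shift of 0.3 SD; baseline correlation r of 0.8-0.9; 2-year replacement risk of 0.5-3%.

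**KL.** Let q be the share entering at grade I and p the probability of moving up one grade. The final-grade proportions are q(1−p) for grade I, qp + (1−q)(1−p) for grade II and (1−q)p for grade III. For n per arm the chi-square noncentrality is λ = n Σ (a−b)²/(a+b), where a and b are the two arms' proportions in a class.

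- q = 0.5: (0.375, 0.500, 0.125) versus (0.450, 0.500, 0.050). λ = 88 × (0.075²/0.825 + 0 + 0.075²/0.175) = 3.43 on 2 df, power 36%.
- q = 0.2: (0.15, 0.65, 0.20) versus (0.18, 0.74, 0.08). λ = 5.28, power 53% (54% by simulation).
- q = 0.8: (0.60, 0.35, 0.05) versus (0.72, 0.26, 0.02). λ = 3.26, power 35%.
- All at one entry grade: the table becomes progressed versus not, and power equals that of the next line.
- Progression from baseline, any mix: λ = 88 × (0.15²/1.65 + 0.15²/0.35) = 6.86 on 1 df, power 74% (75-76% by simulation).

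At an even mix the final-grade test keeps half the noncentrality of the progression analysis (3.43 against 6.86). Grade II holds patients who progressed from I and patients who stayed at II, and the test cannot tell them apart.

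**DXA, 0.3 SD shift, 88 per arm.**

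| Analysis | Power |
|---|---|
| Three-class chi-square, cuts at −2.5 and −1 SD | 18% |
| Three-class chi-square, cuts at −1.5 and 0 SD | 30% |
| Three-class chi-square, cuts at ±0.5 SD | 33% (up to 35% in simulation) |
| t-test on the continuous value, no baseline | 51% |
| ANCOVA, r = 0.8: 0.3/√(1−0.64) = 0.50 SD | 91% |
| ANCOVA, r = 0.9: 0.3/√(1−0.81) = 0.69 SD | over 99% |

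The loss from categorising is the step from 51% to 18-35%. The step from 51% to 91-99% comes from baseline adjustment and must not be charged to the classes.

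**Knee replacement.** 220 × 0.005 = 1.1 and 220 × 0.03 = 6.6, so 1 to 7 events. Even at a control risk of 10%, with the cited 22% reduction, 110 × (0.100 + 0.078) = 19.6 events are expected, and power for that reduction is about 8%.

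**The case against.** Four stronger readings are tempting, and the article does not support them.

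- *The KL analysis is impossible.* Elsewhere the article consistently says severity of osteoarthritis, so the label is probably a slip and the classes may be meant for bone density only. A chi-square on actual KL grades could then be run. What stands is the contradiction in the text and, after the slip is corrected, an unordered test of an ordinal grade without regard to entry grade.
- *The KL test is biased by the entry mix.* Randomisation balances grades I and II in expectation, so the mix adds noise and not bias. The cost depends on the mix and vanishes if all patients enter at one grade.
- *DXA yields no comparison, or would come out null because of the classes alone.* A three-class chi-square is a valid comparison of randomised arms. It is weak and gives no estimate, but most of the gap to ANCOVA is due to baseline adjustment.
- *Treatment arm is excluded from the replacement model.* The article neither names nor excludes it, and a covariate list is commonly left to the analysis plan. What stands is that the stated aim of the model is to find predictors, with no comparison of arms as its purpose.

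It can also be said that these are secondary outcomes without a power claim, and that the article already admits that two years may be short for replacement. Both are true. They limit the weight of the point but do not make the stated analyses fit their outcomes.

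**Conclusion.** The point holds in this form: the KL sentence contradicts the article's own definition of the scale and needs correcting; DXA has a valid but inefficient test with no effect estimate or CI; and knee replacement has no stated comparison of arms. It should be fixed but does not threaten the trial, since the primary WORMS analysis is untouched.

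The sizes are conditional. KL power of about 35-76% against about 75% rests on progression of 25% versus 10% and on the unknown entry mix. The DXA range of 18-35% against 51% rests on a 0.3 SD shift and on the cut-points, and the 91-99% also needs a baseline scan correlated at 0.8-0.9. The 1 to 7 replacements rest on an assumed risk, because the article gives no control-arm risk. No conclusion about the wording depends on these figures.

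**What to change.** 1. Replace the osteoporosis label with osteoarthritis severity, and confine the three density classes to bone density.
2. Analyse KL at 12 and 24 months as progression by at least one grade from baseline, or by a proportional-odds model on grade adjusted for baseline grade. Report the effect estimate with its 95% CI.
3. Analyse DXA separately at each site on the continuous value, as a mean difference with 95% CI, adjusted for baseline where a baseline scan is taken. Keep the classes as description.
4. Report knee replacements as counts per arm with an exact CI for the difference, and label the predictor model exploratory.

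Items 1, 2 and 4 change wording only and use data already planned. Item 3 does too, provided that DXA is done at baseline. Secondary outcomes schedules it only at 12 and 24 months, while Statistical analysis says in general terms that data are recorded at baseline, so this should be confirmed. Without a baseline scan, the unadjusted mean difference with its CI is still available. The changes should be made before unblinding.

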### Outcome measures

#### Primary outcome

Our primary outcome is to determine the improvement in knee structure following each intervention using an MRI-based scale named the Whole-Organ Magnetic Resonance Imaging Score (WORMS) scale at 6 and 12 months after treatment allocation [20]. The WORMS scale is designed to determine the status of the knee joint in patients with OA in respect to fourteen independent articular features. Five out of the 14 features are related to the articular surfaces, and they include: (1) cartilage signal and morphology, (2) subarticular bone marrow abnormality, (3) subarticular cysts, (4) subarticular bone attrition, and (5) marginal osteophytes. In addition, all of these features are further evaluated in 15 different regions divided by anatomical landmarks in a fully-extended knee (Supplementary Fig. 1). For the purposes of our research, we will focus on cartilage signal and morphology. This feature is scored based on only 14 articular surface regions (excluding region S), with a score ranging from 0 to 6 on an 8-point scale (Supplementary Fig. 2). The WORMS scoring system for cartilage includes 0 = normal cartilage thickness and signal, 1 = normal cartilage thickness but with increased signal, 2 = a partial-thickness defect of < 1 cm in the greatest width, 2.5 = a full-thickness focal defect of < 1 cm in the greatest width, 3 = multiple regions having partial-thickness defects alternating with regions of normal thickness or defects > 1 cm, 4 = diffuse partial-thickness defects, 5 = multiple regions of full-thickness defects or defects > 1 cm, and 6 = diffuse full-thickness defects, with an overall score ranging from 0 to 84.

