#### Criteria for discontinuing allocated interventions

Patients who fail to complete the clinical protocol will be considered a dropout of the clinical study. Cases of attrition shall be recorded in detail, and the case report form (CRF) will be kept for future reference. Patients may withdraw spontaneously from the study at any time for any reason without consequences. An investigator may end the patient’s participation if they do not complete follow-up visits or comply with medication treatments. The study will be terminated if significant deviations occur in the design or implementation of the clinical study scheme which makes it difficult to evaluate drug effect. The study will be halted if ordered by the National Medical Products Administration or the researchers decide it is necessary to stop the trial.

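### The only stated missing-data method, survival analysis with last observation carried forward, does not fit a t-test of mean WORMS, so the declared ITT comparison is not secured

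*Protocol article*

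**What the plan says.** All references are to the protocol article.

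- **Endpoint.** The Primary outcome section uses the "Whole-Organ Magnetic Resonance Imaging Score (WORMS) scale at 6 and 12 months after treatment allocation". Only the cartilage feature is scored, "with an overall score ranging from 0 to 84"; higher is worse.
- **Primary analysis.** Statistical analysis states: "Our primary outcome will be analyzed with the intention-to-treat (ITT) analysis". The estimate is a mean difference with 95% CI from Student's t-test.
- **Missing data.** The same section gives one provision: "In order to account for missing data, survival analyses will be conducted while implementing the" LOCF approach. The results go into Kaplan–Meier curves, "showing the numbers of patients analyzed at each assessment timepoint".
- **Ending participation.** The section on criteria for discontinuing allocated interventions lets an investigator end a patient's "participation if they do not complete follow-up visits or comply with medication treatments". Anyone who does not complete the protocol counts as a dropout.
- **Exclusion after randomisation.** Under Study design and setting, unmarketed or other investigational drugs "will be prohibited during the study period; otherwise, such patients will be excluded".
- **Planning figures.** Sample size calculation assumes 4.5% mean annual medial tibial cartilage volume loss, a 2.2% between-group difference at 12 months, and about 10% loss to follow-up each year.

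**The concern.** The method named for missing data belongs to a different kind of endpoint. Kaplan–Meier estimates the distribution of time to an event and deals with censoring. It does not estimate a mean score, and it does nothing for a patient whose 12-month WORMS is absent. LOCF, in turn, has no ordinary role in censored event data. An analyst following the sentence literally would have no instruction for missing values in the primary t-test.

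The likely fallback is to carry the last WORMS forward into the t-test. In a disease that the plan itself treats as progressive, this freezes the score at an earlier, better value. The arm that loses more patients, or loses them earlier, then looks better than it is. Carried values are also treated as if measured, so the standard error is wrong.

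The plan adds to the problem by allowing participation to end because of poor adherence. Missing outcomes can then depend on what happened under treatment, which is what an ITT comparison is meant to guard against.

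**Working it through.** **1. Does any stated outcome need a survival analysis?**

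- WORMS: a score out of 14 regions × 6 = 84, which reproduces the stated range. It is compared by t-test and is not an event.
- Pain, quality of life, bone density, Kellgren–Lawrence grade and biomarkers: chi-square or t-test.
- Risk of knee replacement: event-like, but Secondary outcomes assigns it a multivariable logistic regression.
- Safety endpoints: Cox, Poisson or negative binomial models under Safety analysis, separate from the missing-data sentence.

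So the survival/LOCF sentence is tied to no efficacy event.

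**2. How much data may be missing?** At 10% a year, 10% are missing at 12 months and 1 − 0.9² = 19% at 24 months. (This forecast does not reproduce the rise from 60 to 220 participants: 60/0.81 is about 75. That is a separate matter and does not bear on this point.)

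**3. What would LOCF do if it fed the t-test?** An illustration, under these assumptions:

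- loss is linear over the year, and dropouts follow the same course as completers in their arm;
- annual loss *m* is 4.5 on placebo, and on active 4.5 − 2.2 = 2.3 (planned effect) or 4.5 (no effect);
- *d* is the proportion missing at 12 months. The plan gives only the 10% average; the splits by arm are assumed;
- *f* is the share of the year's loss present at the last scan: 0.5 if that was at 6 months, 0 if at baseline.

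Recorded mean loss in an arm = *m* × [1 − *d*(1 − *f*)]. Benefit = placebo minus active.

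| Scenario | Last scan at 6 months | Last scan at baseline |
|---|---|---|
| True 2.2; 10% missing in both arms | 4.275 − 2.185 = 2.09 | 4.05 − 2.07 = 1.98 |
| No effect; 15% active / 5% placebo | 4.3875 − 4.1625 = 0.225 | 4.275 − 3.825 = 0.45 |
| True 2.2; 15% active / 5% placebo | 4.3875 − 2.1275 = 2.26 | 4.275 − 1.955 = 2.32 |
| True 2.2; 5% active / 15% placebo | 4.1625 − 2.2425 = 1.92 | 3.825 − 2.185 = 1.64 |

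With no effect, the spurious 0.225 to 0.45 is 10% to 20% of the 2.2 target; the reverse split gives the same size against the drug.

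**4. What could that do to the test?** No SD is stated. The one implied by 30 per group, 80% power and two-sided 0.05 is 2.2 / [√(2/30) × (1.96 + 0.84)], about 3.04. At 110 per group the standard error is 3.04 × √(2/110) = 0.41, so the shifts are 0.55 and 1.10 standard errors. Two-sided type I error becomes about 8.5% to 19.5%. At 30 per group it is about 6% to 9%. This depends on the assumed split and the back-solved SD.

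**5. Does the text protect ITT?** The analysis section declares ITT. The discontinuation section is headed as being about interventions, yet its rule ends participation in the study. Study design and setting excludes some patients for a post-randomisation event. The three provisions are not reconciled: the text treats stopping treatment and leaving the study as one thing.

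**The case against.** The case on the other side has several sound parts.

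- **The text never says that LOCF feeds the t-test.** If LOCF stays inside a survival analysis, the figures above do not touch the primary estimate. This stands, and is why both readings are set out. On neither does the sentence deal properly with a missing WORMS.
- **ITT is declared.** A reader might infer that ITT has been abandoned. The documents do not support that: the rule on ending participation is permissive, attrition must be recorded in detail, and nothing removes these patients from the analysis set. With LOCF in the t-test, every patient with an earlier scan would nominally be counted.
- **LOCF need not favour the drug.** A reader might infer that it does, through worse tolerability on active treatment. The plan forecasts no dropout by arm, and the exclusion criteria already remove patients with active ulcers, past upper gastrointestinal bleeding or oesophageal motility disorders. Equal dropout, or more on placebo, works against the drug.
- **The figures are not WORMS points.** The 4.5% and 2.2% are cartilage volume loss, and no WORMS progression rate is given. This stands.
- **Kaplan–Meier could have a proper use,** for instance for knee replacement, which is followed for two years. True, but the plan assigns that outcome another method and offers the curves as the remedy for missing data.
- **The exclusion sentence is narrow.** It covers unmarketed or investigational drugs only, not the NSAID or other-bisphosphonate prohibitions, and no frequency is given. It is minor support.

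Nor is this merely detail left to an analysis plan: the article does state a method, and that method does not suit the endpoint.

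**Conclusion.** The concern holds in this form: the one missing-data method that the article fixes does not fit its primary estimator, and the most natural repair, LOCF in the t-test, contradicts the plan's assumption of continuing cartilage loss. Together with the provisions on ending participation and excluding patients, this leaves the ITT comparison not secured by the stated methods. To say that ITT is not delivered would go further than the text allows.

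The direction and size of any bias are unknown. Under linear loss and a 10% average dropout, the illustrations range from a false benefit of 0.45 with no effect to a true 2.2 reduced to 1.64. The extremes require that every dropout has no scan after baseline. Both ends depend on assumed splits by arm and on the cartilage-volume scale. The mismatch between method and endpoint depends on none of these assumptions.

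**What to change.** 1. In Statistical analysis, remove LOCF and the survival/Kaplan–Meier sentence as the missing-data method. Keep Kaplan–Meier curves only if tied to a defined event.
2. Analyse WORMS in all randomised patients with a baseline-adjusted, likelihood-based repeated-measures model, or with multiple imputation, and report the planned 6- and 12-month contrasts. Add one sensitivity analysis for data missing not at random.
3. Reconcile Study design and setting, Statistical analysis and the discontinuation criteria, so that stopping treatment is kept separate from leaving the study. Already scheduled MRI data should still be collected where consent allows, and patients analysed as randomised. This concerns outcome collection and analysis only; it proposes no rule on when treatment should stop.

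The cost is edits to three sections, slightly more analysis work, and some effort to retain patients for scans that are already scheduled.
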